## Abstract

**Introduction:**

There remains little consensus or guidelines for the clinical management of traumatic orbital fractures (OFx). The OFx Registry aims to increase real-world clinical evidence for the treatment of OFx via prospective, multicentre, international data collection. The primary objectives of this observational cohort study are (1) to document current treatment practices for and (2) to assess the outcomes of surgical and non-surgical treatment of orbital floor and/or medial wall fractures.

**Methods and analysis:**

Approximately 300 adult patients presenting with a displaced OFx in the orbital floor and/or medial wall will be enrolled prospectively over a recruitment period of ~36 months. All eligible patients treated either surgically or non-surgically as per routine standard of care will have follow-up assessments at 6 weeks, 3 months and 6 months post-treatment. Demographic data, injury details, treatment details and outcome measures will be documented in a cloud-based database. Outcome measures include clinical outcomes (eg, diplopia, extraocular motility, and condition of the eyelid, globe and soft tissues), radiological outcomes from collected images, patient-reported outcomes (eg, Diplopia Questionnaire and the newly developed AO Craniomaxillofacial (CMF) Injury Symptom Battery) and complications. A statistical analysis plan will be prepared before final analysis summarising the descriptive statistics to be used for data assessment. Appropriate research questions and statistical tests may be applied additionally, depending on the availability and quality of data collected.

**Ethics and dissemination:**

Ethics approval was obtained before patients were enrolled at each participating site. Patient enrolment followed an informed consent process approved by the responsible ethics committee. Peer-reviewed publications are planned to disseminate the study results.

**Trial registration number:**

NCT03887988.

STRENGTHS AND LIMITATIONS OF THIS STUDYThe study protocol describes a prospective, international, multicentre registry collecting observational, real-world data from a large cohort of patients with fractures of the orbital floor and/or medial wall.By documenting routine standard of care of orbital fractures without intervention, the study will reflect real-world treatment patterns and clinical outcomes across diverse clinical settings.With a planned sample size of approximately 300 patients, the study will have sufficient statistical power for meaningful subgroup analysis, hypothesis generation and generalisability.Limitations of the observational study design include the lack of randomisation and lack of a control group, which limits the ability to establish causality or directly compare treatment effectiveness.Variability in treatment decisions across clinicians and geographical sites may lead to heterogeneity in the data and complex data interpretation but will potentially allow for extensive subanalyses and characterisation of related factors.

## Introduction

 Orbital fractures (OFx) in the craniomaxillofacial (CMF) region may occur after direct blunt trauma to the bony orbit, most frequently by motor vehicle accidents, sports injuries and assaults.^1^,^5^ OFx typically involves the thin bones of the orbital floor (ie, inferior wall) and/or medial wall.^4^ A fracture of the orbital floor and/or walls without a concomitant fracture of the orbital rim is called an orbital blowout fracture.^4^

Diagnosis of OFx via CT and cone beam CT (CBCT) is considered the gold standard method, with CT and CBCT imaging delivering detailed visualisation of the fractures at different angles.^4 6^ OFx can be managed surgically or non-surgically; however, currently, there is no consensus or guideline available on OFx treatment selection depending on defined factors, for example, precise indications for surgical versus non-surgical treatment, the optimal timing of surgery and the best surgical technique.^7^,^13^ Surgical treatment is indicated in cases of retrobulbar haematoma, muscle entrapment, persistent diplopia or clinically disturbing enophthalmos and/or hypoglobus.^14 15^ However, in numerous cases, the indication and timing of treatment is not straightforward because clinical symptoms, for example, duction deficits, and CT scan findings are inconclusive for decision making. In addition, there is conflicting evidence suggesting that surgical treatment may not always lead to better outcomes.^14^ Furthermore, delayed surgery or secondary reconstruction is sometimes necessary, particularly in cases of severe trauma, inadequate initial treatment or progressive anatomical disturbances.^16^,^19^ While surgical treatment aims to restore anatomy and function, it also carries inherent safety risks. Therefore, a decision for surgical treatment should not be made lightly.

These key questions regarding OFx management lack clear answers and characterisation. While recent studies have enhanced the availability of high-quality data and discussions on how patient demographics,^20^ surgical versus non-surgical management^21^ and the timing of surgery^12 22 23^ may impact clinical outcomes, results continue to remain inconsistent and inconclusive. Studies often lack standardised treatment protocols, are single centre, include populations of small sample size and/or demonstrate high heterogeneity in the cohort by failing to account for the diverse presentations of OFx. Furthermore, the long-term functional and aesthetic outcomes of different management strategies remain largely underexplored, limiting the ability to develop evidence-based guidelines.

This international, multicentre registry aims to document the current treatment practices for orbital floor and/or medial wall fractures, including primary treatment and secondary reconstruction, and their outcomes. By identifying and analysing current treatments of orbital floor and/or medial wall fractures, the study will highlight factors influencing clinical success and help determine optimal management strategies. The data collected will increase our knowledge about the treatment of these conditions and potentially may allow us to compare the clinical outcomes of surgical and non-surgical treatments. Additionally, the study aims to investigate the link between radiological parameters, clinical symptoms and treatment choice. The results may help formulate hypotheses, direct future clinical studies, provide better medical and clinical evidence and facilitate clinical decision making of OFx.

## Methods and analysis

### Study design and setting

This is a prospective, multicentre, international, observational cohort study serving as a registry for OFx treatment. Table 1 summarises the sites that are currently included in the study. All sites are academic tertiary care medical centres.

**Table 1 T1:** Details of participating sites

Participating site	Country	Region
Universitätsspital Basel	Switzerland	Europe
University of Belgrade	Serbia	Europe
Hamad Medical Corporation	Qatar	Middle East
King Edward VIII Hospital	South Africa	Africa
Medizinische Hochschule Hannover	Germany	Europe
Rambam Health Care Campus	Israel	Middle East
12 de Octubre University Hospital	Spain	Europe
National Medical and Surgical Center named after N.I. Pirogov	Russia	Europe and Asia
Ludwig-Maximillians-Universität – Klinikum der Universität München	Germany	Europe
Federico II University of Naples Italy	Italy	Europe
Erasmus University Medical Center	Netherlands	Europe
University of California, Davis	USA	North America

### Objectives

Aside from collecting standard of care data into a large registry database and increasing our knowledge about the treatment and outcome of OFx, the specific objectives are (1) to document the current practice in both the primary and secondary treatment for orbital floor and/or medial wall fractures and (2) to describe and compare the outcomes of surgical and non-surgical treatment of orbital floor and/or medial wall fractures.

### Study design

This observational study protocol does not dictate any study-specific treatments, selection of materials or surgical techniques. All treatments will be performed according to the usual practice at participating sites and determined by the treating surgeons. Patients will be allocated to either the surgical or non-surgical group based primarily on local standard of care practices. This decision will be guided by the treating clinician’s judgement and relevant clinical indications, including individual patient characteristics and patient willingness to receive treatment. Post-treatment care and follow-up visits will also be conducted according to the standard procedures at participating sites.

Non-surgical treatments include either observation only, that is, no treatment or specific measures given, or conservative treatment with the use of supportive measures, for example, local antibiotics, anti-inflammatories, cold compresses and head elevation.

Primary surgical treatments will be classified as either ‘early’ or ‘delayed’ surgery when performed at ≤3 weeks or >3 weeks after the injury, respectively. Secondary reconstructions following unsuccessful primary surgical treatments of OFx will also be included in the study.

#### Inclusion criteria

Age 18 years or older at the time of the injury.Patients with a displaced fracture of the orbital floor and/or medial orbital wall (areas 9, 10, 11, 15 and 16 according to the AO CMF Fracture Classification System,^24^ either diagnosed at the study site via CT or CBCT within 2 weeks of the injury or undergoing secondary reconstruction.Signed and dated Ethics Committee/Institutional Review Board (EC/IRB) approved written informed consent. For patients who are unable to provide independent written informed consent, written consent will be obtained according to the EC/IRB approved procedures.

#### Exclusion criteria

Bilateral orbital fracture.Concomitant displaced fracture(s) of the orbital roof or any other area of the orbit.Concomitant ruptured globe.Displaced fracture of the malar bone.Displaced midface fracture.Displaced naso-orbito-ethmoid fracture or complex zygoma fractures.Presence at the time of enrolment of any disease with influence on eye motility (eg, strabismus, myasthenia gravis, Graves’ ophthalmopathy).Previous radiotherapy in the orbital region.Participation in any other medical device or medicinal product study within the previous month(s) that could influence the results of the present study.

#### Recruitment

The recruitment period will be ~36 months, during which approximately 300 patients are planned to be enrolled.

The participating sites will identify all consecutive eligible patients according to the defined inclusion and exclusion criteria. Eligibility assessment will be performed by the investigator and/or adequately trained member(s) of the research team. The assessment of eligibility includes but is not limited to an inquiry about the interest and willingness of the patient to participate in the research project. Data collection for this registry is not allowed without the consent of the patient or surrogate, and therefore, no data are collected in the electronic case report form (eCRF) prior to obtaining consent by the patient.

All consented patients will be allocated to a unique patient number. Each site will keep an Identification List linking the patient number with his/her personal information. Such Identification List is kept safe and in a locked place always. Sites are not allowed to share the Identification List with any third party except for the sponsor representative, legal authorities and EC/IRB, who may have access to the Identification List during monitoring/auditing activities performed on-site.

All consented patients should be followed up within the registry, except if their study participation is prematurely terminated.

#### Data collection

##### Baseline information

Demographic data (gender and year of birth) and medical history (eyelid disorders, globe asymmetry, visual field defects or blindness, and diplopia prior to the trauma) will be recorded for each patient.

##### Injury details

Injury details such the date of injury, mechanism, side of fracture, affected anatomical area, fracture characteristics (linear/defect), the dimensions of defect type fractures (maximum diameters in the anterior-posterior and lateral-medial directions) and the involved structures (nasolacrimal duct, lacrimal bone, internal orbital buttress (anterior and/or mid orbit), and the position and form of the rectus inferior muscle) will be recorded.

If a patient had primary reconstruction prior to enrolment, details on the primary implant and additional injury details such as the concurrent additional fractures, visual acuity, condition of the globe and its mobility, and the status of the eyelid will be documented as fully as possible.

##### Treatment details

For non-surgical treatment, the treatment date will be documented as the date of diagnosis.

Surgical details to be documented depending on whether it is primary or secondary reconstruction but may include the following as appropriate:

Indications.Date of surgery.Time (in days) from trauma to surgery.Factors affecting timing of primary reconstruction, such as implant-related factors, hospital-related factors and clinical reasons.Surgery time (from skin incision to wound closure).Whether a forced duction test was performed.Surgical approach.Type of retractor used.Type(s) and material(s) of primary and secondary (if applicable) implant(s) used.Whether previous implants were removed.Use of computer-assisted methods for preoperative planning and/or intraoperative navigation.Use of antibiotics and steroids.Use of intraoperative imaging.Periorbital release, stripping and additional soft tissue procedures.

For patients who had primary reconstruction prior to enrolment, the primary treatment details will be documented as completely as possible.

##### Imaging data

Each site will take images and clinical pictures according to the local standard of care (routine) procedures. All images and pictures taken will be de-identified and sent to the sponsor.

##### Follow-up schedule

In general, patients will be followed up counting from Day 0 at approximately 6 weeks, 3 months and 6 months, as conforming to the routine visit schedule at the study site. These patients will remain active in the study for 6 months unless they received additional treatments.

The definition of ‘Day 0’ is different for different patients. For patients with acute fractures, if the patient:

is treated non-surgically, Day 0 is the day of the diagnosis.is treated with primary ‘early’ or ‘delayed’ reconstruction, Day 0 is the day of the surgery.is treated with secondary reconstruction within the registry but had a primary reconstruction prior to enrolment, Day 0 is the day of the first surgery performed within this registry.is treated with primary reconstruction within the registry but then requires secondary reconstruction, Day 0 remains the day of the primary reconstruction and will not be shifted. The patients will be followed up at approximately 6 months after the secondary reconstruction according to the site’s routine visit schedule. These patients will remain active in the study for 6 months from the secondary reconstruction or up to the maximum of 1 year since Day 0.For patients needing more than one surgery within this study, they will remain active in the registry for 6 months after the last surgery but with the limit of maximally 1 year counting from Day 0.

The schedule for data collection at each visit is summarised in table 2.

**Table 2 T2:** Schedule of follow-up visits and data collection

	Baseline	Treatment	Post-treatment visit 1	Post-treatment visit 2	Post-treatment visit 3	Additional treatment
	–	Day 0	6 weeks (+14 days)	3 months (+14 days)	6 months (+14 days)	Any time during follow-up
Eligibility	X					
Patient information/consent	X*					
Demographics and medical history	X					
Injury details	X					
Treatment details		X†				X
Clinical and functional outcomes	X‡		X	X	X	
Patient-reported outcomes	X§		X	X	X	
Adverse events/complications	X	X	X	X	X	X
Images (eg, CT, CBCT, X-rays)	X¶	X¶	X¶	X¶	X¶	X¶

* Informed consent may occur after treatment under certain circumstances (eg, treatment is immediate emergency, patient has temporarily impaired decision-making capacity, patient is unable to give written consent due to their injuries). No data can be collected in the eCRF prior to consent.

† For patients who undergo primary ‘delayed’ surgery, the Day 0 is considered as the day of the surgery.

‡ Clinical and functional outcomes at baseline refer to the status post injury and prior to treatment.

§ Patient-reported outcomes at baseline refer to the status post injury and prior to treatment.

¶ Only images (CT, CBCT, X-ray, etc) taken as part of the standard of care procedures will be collected. All images and pictures are de-identified.

CBCT, cone beam CT.

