### Termination of participation

Patient participation in the study may terminate for reasons such as withdrawal of informed consent, ineligibility (screening failure), failure to commence treatment within this registry, loss to follow-up, death and termination of participation by the sponsor. Detailed information explaining the circumstances leading to the termination will be recorded in a dropout form. For these patients, the collected data will be censored as the day of termination and may be used in the analysis.

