### Statistical analysis

This is a registry-style observational study that aims to increase our knowledge about the treatment and outcome of OFx. Therefore, there is no formal statistical hypothesis and no formal sample size calculation. However, a detailed statistical analysis plan will be prepared before the final analysis documenting the descriptive statistics to be used for data assessment.

As the aim of the current registry is mainly descriptive, the patient characteristics, clinical data and outcomes recorded at routine standard of care scheduled follow-up assessments will be presented using simple summary statistics. Categorical variables will be summarised using the frequency and percentage for each category. Continuous variables will be summarised using the mean, SD, median, IQR, and minimum and maximum. Additionally, these summary statistics will be presented according to clinically relevant categories, for example, according to treatment received (conservative vs surgical treatment). Depending on the volume and the quality of the collected data, further appropriate statistics will be applied.

The AEs will be summarised both at patient level and AE level. AE rates with 95% CIs will be calculated based on the total population size, irrespective of dropouts during follow-up.

In general, all enrolled and eligible patients who were treated within the registry will be included in the analysis. If a patient discontinues participation due to any reason, all data collected before discontinuation will be integrated into the analysis. For specific research questions, only certain subgroups of patients may be relevant. In such a case, prior to the analysis, it will be defined which patients will be included in the analysis. Details concerning the handling of missing data and protocol violations will be specified in the statistical analysis plan.

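### Day 0 and treatment group both depend on later surgery, so the surgical versus non-surgical comparison can shift poor responders out of the non-surgical group and compare same-named visits at different times since injury

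*Protocol article*

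**What the plan says.** The Objectives section of the protocol article includes comparing outcomes between surgical and non-surgical treatment. These rules determine how that comparison is made:

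- **Clock, non-surgical (Follow-up schedule).** If an acute patient "is treated non-surgically, Day 0 is the day of the diagnosis".
- **Clock, surgical (Follow-up schedule and Table 2 footnote).** Day 0 for primary surgery is the operation. The footnote repeats this for primary delayed "surgery, the Day 0 is considered as the day of the surgery".
- **Failed primary reconstruction (Follow-up schedule).** Here "Day 0 remains the day of the primary reconstruction and will not be shifted". No matching sentence covers a patient observed first and operated on later.
- **Eligibility (Inclusion criteria).** Acute fractures must be "either diagnosed at the study site via CT or CBCT within 2 weeks of the injury".
- **Early and delayed (Study design).** Primary treatment is early or delayed "surgery when performed at ≤3 weeks or >3 weeks after the injury, respectively".
- **Non-surgical care (Study design).** It includes "observation only, that is, no treatment or specific measures given".
- **Grouping (Statistical analysis).** Summaries are to be shown by clinically relevant category, the example being "according to treatment received (conservative vs surgical treatment".

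The Introduction lists persistent diplopia among the indications for surgery. Table 2 has a column for additional treatment at any time during follow-up.

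**The concern.** Group and time origin are both settled by what happens after diagnosis. A patient who is observed, does not improve and is then operated on late has received care that meets the protocol's own definition of non-surgical treatment. If the footnote is followed, that patient's clock restarts at surgery and the treatment-received table counts the patient as surgical. Since persistent symptoms are a reason to operate, such moves are related to the outcome being compared.

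Two distortions of objective 2 follow. The non-surgical group can lose some of its poor responders. Delayed-surgery patients are also seen later after injury at visits that carry the same name, with more time for natural recovery. The first distortion flatters non-surgical care and the second may flatter surgery, so the net direction is not known in advance.

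**Working it through.** The protocol article gives no calculation on this point, so there is no figure to reproduce.

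**Step 1: time since injury at each visit.** Inputs: diagnosis 0 to 14 days after injury (Inclusion criteria); early surgery up to day 21 and delayed surgery from day 22 (Study design); visits at 6 weeks, 3 months and 6 months, taken as 42, 91 and 182 days, each with a window of up to +14 days (Table 2). Formula: days since injury = Day 0 offset + visit day + 0 to 14.

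| Group | Day 0 offset | 6-week visit | 3-month visit | 6-month visit |
|---|---|---|---|---|
| Non-surgical | 0–14 | 42–70 | 91–119 | 182–210 |
| Early surgery | 0–21 | 42–77 | 91–126 | 182–217 |
| Delayed, earliest | 22 | 64–78 | 113–127 | 204–218 |
| Delayed, day 90 (illustration) | 90 | 132–146 | 181–195 | 272–286 |

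Early surgery exceeds the non-surgical upper bound by 77 − 70 = 7 days, which matters little. Delayed surgery has no upper bound. With surgery on day 90, the 6-week visit (132–146) is later after injury than any non-surgical 3-month visit (91–119).

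**Step 2: the patient who fits both rules.** Diagnosis is by day 14 and delayed surgery is after day 21, so every acute delayed-surgery patient is unoperated for more than 21 − 14 = 7 days after diagnosis. For surgery on day 90, the two readings give:

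- Day 0 at surgery: the 6-week visit falls on days 132–146, after the operation.
- Day 0 at diagnosis, with surgery entered as additional treatment: the 6-week visit falls on days 42–70, before the operation.

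The same patient's 6-week result is thus post-operative or pre-operative depending on the reading.

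**Step 3: what reclassification could do.** The documents give no rates, so all of these are assumptions. Take 300 patients, half initially non-surgical, with the same failure risk p = 20% in both groups when conversion counts as failure. A share c = 50% of non-surgical failures converts and nobody else does. Let r be the share of converters still failing after surgery.

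- Converters: x = 150 × 0.20 × 0.50 = 15.
- As-treated non-surgical risk: p(1 − c)/(1 − pc) = 0.10/0.90 = 11.1%.
- As-treated surgical risk: (30 + 15r)/165 = 18.2% at r = 0 and 27.3% at r = 1.
- Apparent gap: 7.1 to 16.2 points.

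Over p = 10–30%, c = 25–75%, a non-surgical share of one third to two thirds and r = 0 to 1, the gap runs from 1.8 to 42.0 points. It always favours non-surgical care, because the illustration lets only failures convert.

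With converters kept in their initial group, conversion is 15/150 = 10%. Failure or conversion is 30/150 = 20%, equal to the surgical 30/150 = 20%. Final status alone is (15 + 15r)/150 = 10% to 20%. Final status therefore needs to be read together with the conversion rate.

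**The case against.** The best defence is that Day 0 is a visit schedule rather than an analysis time origin. Treatment received is offered only as an example of a grouping, the registry is mainly descriptive with no formal hypothesis, and the SAP, which is not shown, may set a time scale and a crossover rule. The article also concedes the lack of randomisation and a control group, and expects treatment-strategy bias. Much of this stands: it limits the harm to objective 2 and leaves room for repair in the SAP. It does not dispose of the point. The conflicting Day 0 rules are stated in the article, visits follow Day 0, and the acknowledged limitations do not mention time origin or reclassification.

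It also stands that not every delayed operation is a failure of observation. Treatment details lists implant and hospital reasons for timing as well as clinical ones.

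A reader might infer more than the documents support:

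- *The bias cannot be untangled afterwards.* Date of injury, days from trauma to surgery and the factors affecting timing are all recorded, so patients can be regrouped.
- *This is immortal-time bias.* The surgical clock starts at surgery, so no event-free time before the operation is credited to it. The issue is selective reclassification.
- *Patients who improve and are never operated on fall out of both groups, because "failure to commence treatment within this registry" is a ground for termination.* Observation is itself treatment and is dated at diagnosis, so such a patient has already commenced treatment. Data from terminated patients may also be used.

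**Conclusion.** The point holds for acute fractures. Followed as written, the comparison in objective 2 can move poor responders from the non-surgical to the surgical group and set visits of the same name at different times since injury. The timing half follows from the stated rules by arithmetic: 42–70 days against at least 64 days at the 6-week visit. It concerns delayed surgery, with early surgery hardly affected. The reclassification half comes from reading the Day 0 rules, the footnote and the grouping together. The additional-treatment column leaves another reading open, so the text does not establish that the non-surgical group is stripped of all its failures.

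The size of the bias is unknown. It depends on how many patients convert, why, and how they fare, none of which the documents give. The 1.8 to 42.0 point range shows only what the assumed rates imply and is not an estimate for this registry.

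**What to change.** Reconcile the Day 0 and grouping rules for patients observed first and operated on later, so that all 12 sites record them alike. Then, before the final analysis, specify the surgical versus non-surgical comparison as follows:

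1. Restrict it to acute fractures. Exclude patients enrolled for secondary reconstruction, whose time since injury has no limit.
2. Classify by operated or not at a landmark of 3 weeks after injury, the registry's own early/delayed cut.
3. Keep patients operated on after the landmark in the initially non-surgical group.
4. Report conversion to delayed surgery as an outcome of that group, with the recorded reason for timing.
5. Report, or adjust for, actual time since injury at each visit.
6. Keep the as-treated table as secondary.

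The cost is protocol and SAP wording plus modest analysis work, since the dates and timing reasons are already collected. The landmark (day 21) precedes the earliest possible 6-week visit (day 42). There are two drawbacks. The initially non-surgical group will contain some patients operated on later. Delayed-surgery patients may also have no scheduled visit at the matching time since injury, which regrouping cannot supply.
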